### Study design overview

A prospective effectiveness-implementation hybrid design [70] involving pre-post intervention evaluation with matched controls will be used to implement and evaluate the HKTP. Due to design, matched control sites were pre-specified, and were matched with intervention sites based on city population size, Hispanic proportion of the city population, and kidney transplant and LDKT volumes. Although an ideal study design would be a randomized controlled trial that randomizes patients within each center, it is laden by contamination effects. Randomizing at the center level would require a large number of centers to serve as intervention sites and controls, which is costly. To assess other secular trends, data from matched control centers that do not implement the HKTP will be compared. Control sites were selected in different cities than intervention sites to avoid contamination from local implementation efforts. The first year will focus on implementing the HKTP at BUMC and MC over a 12-month period (Aim 1). Remaining years will focus on evaluating the HKTP on Hispanic LDKTs and on program fidelity in years 2–4½ (Aims 2 and 3).

The hypotheses are that the HKTP will lead to a(n):H_1_ Increase in the ratio of Hispanic to non-Hispanic white LDKTs and in the number of Hispanic LDKTsH_2_ Increase in the number of Hispanic ESRD patients added to the waiting listH_3_ Increase in the number of Hispanic potential donors per potential recipientH_4_ Greater satisfaction of Hispanic ESRD patients with culturally competent care

AIM 1: To implement the HKTP at Two Transplant Centers.

The NU team will first provide BUMC and MC with a preliminary set of protocols comprising the HKTP manual of operations, scripts for clinical coordinator and outreach staff to use, and educational materials describing the structure and content of the education sessions and transcriptions. To train the staff and providers at BUMC and MC, a video-based curriculum will be provided that explains the outreach staff’s communications with dialysis patients, and demonstrates NM’s HKTP Director’s education sessions. NM’s HKTP education session PowerPoint slides will also be provided for sites to use. The set of protocols will help BUMC and MC to determine how to modify their organizations to accommodate the HKTP. Publications that provide evidence to support the HKTP’s increase in Hispanic LDKTs will be provided to foster site ‘buy in’ to implement the HKTP [20, 68].

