*Site Visit* [name] and [name] (co-PIs) will conduct a site visit in year 1 to perform the needs assessment to identify transplant provider-, administrator-, and center-related barriers and facilitators to the implementation and sustainability of the HKTP, in order to refine and deliver the final set of protocols, scripts, and educational materials. During the needs assessment, [name] will use ethnographic methods [71] to interview, observe, and survey BUMC’s and MC’s transplant physician (and/or site-PI), staff (outreach staff), and administrators involved in HKTP implementation (total n = ~ 5 per site).

*In-Depth, Qualitative Interviews* will assess the current workflow and where changes could be made within the workflow to comply with the HKTP protocol. Interviews will be audio-recorded and last 30–45 min.

*The “Learning Collaborative”* [72, 73] method will be used to help BUMC and MC staff design center-customized approaches and solutions to barriers to implementing the HKTP. This short, rapid approach to healthcare quality improvement is often used by organizations and providers to work collaboratively by sharing their experiences and best practices to accelerate learning [74, 75]. This approach can increase critical thinking and leadership skills more than individual learning [76, 77], and enhance the observability and trialability of the HKTP -- characteristics identified as important in Revised PARIHS evidence framework. Staff from BUMC and MC will visit the NU research team in month 7 for a 2-day “learn together” program [78] to discuss their challenges and strategize on overcoming problems with implementing the HKTP at their institutions. During the in-person meeting, BUMC and MC staff will shadow and role-play with NU staff to practice communicating with patients and responding to patients’ questions. Additionally, the Learning Collaborative will entail routine telephone calls between program staff to benchmark against each other and NM’s HKTP to identify best practices and learn from one another. The NU research team will continuously help troubleshoot ways that BUMC and MC can increase readiness and adapt the HKTP into their programs, using NQF guidelines and the cultural competence analytic framework [65, 69]. Through collaborative learning, BUMC and MC staff will obtain the social support necessary to overcome isolation of going through the implementation process alone.

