Based on data analysis of the needs assessment, a subsequent, final set of protocols, scripts, and materials that integrate modifications to the HKTP that adapt the HKTP to each intervention site will be created and provided. Remediation plans will be used to assist intervention sites in implementing the protocols, as needed, if deficiencies are detected by the research staff or observed during site visits.

Formative evaluation procedures will be used to optimize intervention implementation (fidelity) [79], and enhance the HKTP, as the NIDDK program announcement requires [80]. Specifically, the delivery of *dosage* and *coverage* of required programmatic elements will be evaluated to determine whether all intervention components were implemented as planned, and to identify which parts of the HKTP worked best. Monitoring will occur weekly during implementation (months 0–8), twice per month for adjustment (months 9–12), and monthly for process checks (months 13–54). Given that people’s actions typically differ from what they say they do [71], we will use mixed methods [81] to assess actual behaviors.

AIM 2: To evaluate how factors from the CFIR and the Revised PARIHS frameworks and emergent factors unique to the implementation of culturally competent care affect fidelity.

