*Organization surveys* will assess BUMC’s and MC’s readiness to change, facilitation capacity, and disposition to accepting evidence about the HKTP’s effectiveness to implement change, using the validated, Organizational Readiness to Change (ORCA) instrument (Cronbach’s alpha = 0.74–0.95) [84]. ORCA surveys will be self-administered on paper by the clinical team and research staff before the first site visit.

*Online surveys* will be completed by the research staff (via Research Electronic Data Capture (REDCap)) that assess metrics about key HKTP components on a monthly, quarterly, or biannual basis based on observation or information provided by the outreach staff. For example, the frequency of outreach visits to dialysis centers per month, the number of Hispanic patients met per visit, the number of patients who express an interest in coming to the HKTP for evaluation per visit, the number of these patients who share their contact information with the outreach staff, the number of these patients who schedule an appointment, the number of patients who show up to each HKTP education session, the number who complete the evaluation process and get waitlisted for transplantation, and the number who get a transplant by type of transplant. Additionally, the research staff member will track through online surveys the number of HKTP education sessions per month, and marketing efforts. Finally, research staff will assess whether their hospital’s patient advocacy department has received any concerns from patients or families with the HKTP program on a quarterly basis through a single-item survey.

*Observations* will be conducted in two ways. (1) During the site visits, [name] will conduct observations of the dialysis outreach, telephone communications, and educational sessions in practice to see how they occur and to learn about the organizational culture. (2) During routine intervals, research staff will shadow outreach staff as they perform outreach at dialysis centers, and observe faculty delivering the education sessions monthly (months 13–54) to identify potential discrepancies from the HKTP protocols and scripts to amend.

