### Outcome measures

We will assess the reduction in disparities between self-identified Hispanics and non-Hispanic whites in LDKT rates for adult-to-adult living kidney donation. The effectiveness of the HKTP will be assessed by comparing the outcomes before introducing the HKTP and after the HKTP has been fully implemented. Measures will be collected at intervention and control sites in pre and post periods. For the final outcome measures, de-identified, aggregate center-level data will be collected from the Organ Procurement and Transplant Network/United Network for Organ Sharing (OPTN/UNOS) as publically reported data (Table 2). Data from sites’ medical record review will also be collected. Intermediate outcome measures about each Hispanic and non-Hispanic white potential recipient and potential donor will be collected monthly by research directly from intervention and control sites by medical record review to assess the pathways by which the HKTP potentially increases rates of Hispanic LDKT. We expect that the pre-post change will demonstrate a higher number of potential donors who initiate evaluation and complete more steps in the donor evaluation process.

**Table 2 Tab2:** Final and Intermediate outcome measures: transplant center-reported

Construct	Measure description
Final outcomes	
Ratio of Hispanics to Non-Hispanic Whites Receiving LDKTs	This ratio takes into account growth in transplant center volume while also providing a comparison to non-Hispanic whites, necessary for assessing disparities in LDKT [102]. The ratio provides an index of whether the Hispanic LDKT increase has grown over and above the increase observed at a center overall. By using this ratio, factors related to the center’s infrastructure and capacity to perform additional LDKTs that affect both Hispanics and non-Hispanic whites equally are accounted for. Institutional commitments to LDKT that are associated with higher rates of LDKT, can influence willingness to donate or preferences for LDKT, and affect both populations equally (e.g., paired donation, and desensitization efforts), are accounted for.
Number of Hispanic LDKTs	Change in number of Hispanic LDKTs compared to change in number of non-Hispanic white LDKTs will provide evidence that the increase is not at the expense of white patients.

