Hispanic patients’ and family members’ satisfaction with culturally competent care will be evaluated before and after implementing the HKTP by using the validated, closed-ended, DHHS AHRQ Consumer Assessment of Healthcare Providers and Systems (CAHPs) Cultural Competence Item Set (34 items) [93, 94] and Patient Centered Medical Home subset (8 items) [88, 89]. Topics covered include: patient-provider communication, shared decision making, preferences for shared decision making, experiences leading to trust or distrust, experiences of discrimination, and linguistic competency. Surveys will be self-administered on paper in the clinic waiting room after completing clinic visits that day. A total of *n* = 70 patients/donors will be surveyed at each site in year 1 (pre-HKTP) and year 5 (post-HKTP) [93], in English or Spanish [95].

Contextual measures will also be collected from all sites to control for confounders through routine phone call communications with study sites. News items and policy changes will also be scanned for secular effects on data collection or HKTP outcomes. For example, the research team will take note of international, national, regional, and hospital news items pertaining to health disparities, Hispanics, and/or organ transplantation/donation.

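### The year-1 satisfaction baseline is labelled pre-HKTP but falls in the HKTP implementation year, and no cut-off keeps exposed respondents out of it

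*Protocol article*

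**What the plan says.** The Outcome measures section places the two satisfaction waves by calendar year: patients and donors are "surveyed at each site in year 1 (pre-HKTP) and year 5 (post-HKTP"). They fill in the questionnaire in the clinic waiting room after that day's visit. The same section gives the general contrast for effectiveness as "comparing the outcomes before introducing the HKTP and after the HKTP has been fully implemented".

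The Study design overview describes year 1 differently: "The first year will focus on implementing the HKTP at BUMC and MC over a 12-month period". Under Aim 1 it divides the study into phases: "Monitoring will occur weekly during implementation (months 0–8), twice per month for adjustment (months 9–12), and monthly for process checks (months 13–54"). Within year 1, "Staff from BUMC and MC will visit the NU research team in month 7 for a 2-day" joint learning programme.

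The Statistical analysis plan section compares CAHPS composite scores between the two waves, separately by site, with a two-sample t-test. It claims 80% power from 50 respondents before and 50 after, for a difference of 10% with SD 18% and two-sided alpha 0.05.

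**The concern.** One calendar year carries two labels. For the survey it is the time before the HKTP; for the rest of the study it is the time in which the HKTP is put in place. The article gives no date for first patient contact, no month by which the baseline survey must close, and no rule that keeps people who have already met the programme out of the pre group.

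Several components can reach a patient before an HKTP clinic is running: dialysis-centre lobby days, the scheduler script and the Spanish telephone line. The survey covers linguistic competency and patient-provider communication, which such components are meant to improve. Hypothesis 4 rests on a plain difference between two cross-sections, so any exposed respondent counted as pre raises the baseline mean and shrinks the difference, provided the HKTP works in the direction that the hypothesis states.

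**Working it through.** **Step 1. Set the timeline side by side.**

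| Item | When | Section |
|---|---|---|
| Baseline survey, labelled pre-HKTP | Year 1 | Outcome measures |
| Implementing the HKTP | Year 1, 12 months | Study design overview |
| Monitoring phase: implementation | Months 0–8 | Study design overview, Aim 1 |
| Staff visit for training | Month 7 | Study design overview, Aim 1 |
| Monitoring phase: adjustment | Months 9–12 | Study design overview, Aim 1 |
| Monthly process checks | Months 13–54 | Study design overview, Aim 1 |
| Intended contrast | Before introduction against after full implementation | Outcome measures |

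All of year 1 lies inside the implementation and adjustment phases. The Aim 1 text also ties the monitoring, weekly from month 0, to the delivery of dosage and coverage of programme elements. Nothing separates the baseline survey from these activities.

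**Step 2. Reproduce the plan's power.** Inputs from the Statistical analysis plan section: n = 50 per wave, difference 10, SD 18, two-sided alpha 0.05.

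- Standard error = 18 × √(2/50) = 3.60
- Noncentrality = 10 / 3.60 = 2.78
- Power = 78.5% (exact t, 98 df) or 79.3% (normal approximation)

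The stated 80% is reproduced. With 70 per wave (the survey number in Outcome measures, read as 70 in each wave), the standard error is 18 × √(2/70) = 3.04 and power is 90.4%.

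**Step 3. Illustrate the dilution.** Let f be the share of baseline respondents already exposed. The document gives no value for f, so a range is shown. Assume that each exposed respondent already has the full 10-point effect.

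- Expected pre-post difference = 10 × (1 − f)
- SD held at 18; letting the mixture widen the baseline SD lowers power by about 1 point

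| f (assumed) | Difference | Power, 50 per wave | Power, 70 per wave |
|---|---|---|---|
| 0 | 10.0 | 78.5% | 90.4% |
| 10% | 9.0 | 69.7% | 83.6% |
| 25% | 7.5 | 54.1% | 68.7% |
| 50% | 5.0 | 28.0% | 37.2% |

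At 70 per wave, power falls below 80% once f exceeds about 14%.

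**Step 4. Relax the full-effect assumption.** If exposed respondents have half the effect (also an assumption) and f = 25%, the difference is 10 × (1 − 0.25 × 0.5) = 8.75. Power is then 67% with 50 per wave and 81% with 70.

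**The case against.** The strongest reply is that a clean baseline is plainly intended. The wave is labelled pre-HKTP, and the Outcome measures section sets the comparison against the time before introduction. Much of what the article describes for year 1 is preparation: needs assessment, handing over protocols, and training. Research staff "observe faculty delivering the education sessions monthly (months 13–54"), which is 54 − 12 = 42 months. That matches the 14 post-intervention quarters (14 × 3 = 42) and the evaluation period of years 2 to 4½. On this reading year 1 is set-up, and a survey done early in it would be uncontaminated. A closing date is also the kind of detail that an article may leave to the full protocol.

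Most of this stands as a limit on the claim. A reader might infer that the baseline will be contaminated, or that the programme is already running with patients in months 9–12. The document does not support either: it dates no lobby day, telephone line, scheduler script or clinic, and the word adjustment does not establish that patients are being seen.

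What the reply does not remove is the conflict. Starting the counted post period at month 13 makes year 1 a transition year; it does not make months 1–12 unexposed. The article has not merely left out a date. It fixes a window, calls it pre-HKTP, and elsewhere gives that same window to implementation.

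**Conclusion.** The point holds as a conflict in timing. The baseline window, as written, permits exposed respondents to be counted as pre-HKTP, contrary to the plan's own contrast. The bias in the hypothesis 4 difference would be toward zero, on the assumption that the HKTP raises satisfaction.

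The amount cannot be stated. Under the full-effect illustration, each 10% of exposed baseline respondents removes 1 point from the planned 10-point difference, and the power figures follow from that. They show sensitivity and do not forecast this study's loss. Losses are smaller if early contact has only part of the effect, and there is none if the survey closes before patients meet any component.

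Two stronger readings should be resisted. The 80% power figure is not wrong on its own inputs. Nor is the problem beyond repair once data are in: where survey date and exposure are known for each respondent, exposed ones can be taken out of the pre group. The article, however, does not say that these will be recorded. The point concerns hypothesis 4 only and does not touch the analysis of transplant numbers and ratios.

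**What to change.** Define the baseline by event instead of by calendar year:

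- At each intervention site, close the pre-HKTP survey before the first HKTP component reaches patients, whether that is a lobby day, the Spanish telephone line, the scheduler script or a clinic.
- Record the survey date and any HKTP exposure for every respondent.
- Exclude respondents with exposure from the pre group. This also covers surveys already taken later in year 1.
- Reconcile the year-1 label in Outcome measures with the implementation phases in the Study design overview.

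The change needs a sentence or two on the survey window and two recorded items per respondent. The downside is a shorter baseline window and possibly slightly fewer baseline respondents.

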### Statistical analysis plan

SAS version 9.4 (Carey, NC) will be used for analyses. Testing of each hypothesis will be performed separately for each study site. For Hypotheses 1 and 2, quarterly UNOS outcome data (6 years pre- and 3.5 years post-HKTP) will be used to model ethnic and racial differences in transplants, to account for external events that could alter LDKT rates, and to analyze the sustainability of the HKTP intervention. Hypotheses 3 and 4 will be evaluated with monthly data. Associations between final outcome and intermediate outcome measures, and individual patient and donor level variables will be evaluated. Matched intervention and control sites will be compared.

To test hypothesis 1, we will use OPTN/UNOS data, to construct the ratio of the number of Hispanics receiving LDKTs to the number of non-Hispanic whites receiving LDKTs for each center from 6 years prior to 3.5 years after implementation of the HKTP. An interrupted time series (ITS) design with segmented regression analysis will be used to assess the HKTP. Ratio data will be collected across 24 quarterly time points pre-intervention (reference point), and 14 time periods post-intervention for a total of 38 time-series data points for each center.

A probabilistic sensitivity analysis will be conducted to ascertain the likelihood that changes in the volume of LDKTs at study sites are indeed attributable to implementation of the HKTP. Rather than assigning a single value to each parameter, we will assign a distribution to all parameters in the model. The ranges will be determined by the average value, the standard deviation, and the shape of the spread of the data. A 1-way sensitivity analysis by varying one parameter at one time will be used to identify secular trend threshold values. We will collect intermediate outcome data at control sites to enable more nuanced pretest-posttest analyses. Sensitivity analyses using published [96, 97] and publically reported LDKT volume data from matched controls will be used to adjust for regional variability. In addition, the two transplant centers implementing the HKTP will be compared to each other. To assess the influence of innovative adaptations on outcomes, qualitative data from routine assessments of the modifications to the HKTP (Aim 2), collected at 14 quarterly time periods post-intervention, will be transformed into quantitative parameters, and will be incorporated into a longitudinal data analysis evaluating trend in outcomes over the post-intervention period accounting for quarterly time-varying adaptations.

We expect an increase in satisfaction scores before and after the education sessions by 10% in post-HKTP based on prior studies [98]. Differences in CAHPS composite scores will then be compared between pre- and post-HKTP by each site using a two-sample t-test. A total of 100 patients per site (50 pre-HKTP, 50 post-HKTP) provides 80% power to detect a difference of 10% (SD = 18%) in mean satisfaction scores before and after education sessions between pre- and post-HKTP groups using a two-sided t-test with a *p* = 0.05 significance level.

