**Methods/Design:**

Using a prospective effectiveness-implementation hybrid design involving pre-post intervention evaluation with matched controls, we will implement a complex culturally targeted intervention at two transplant centers in Dallas, TX and Phoenix, AZ. The goal of the study is to evaluate the effect of Northwestern Medicine’s® Hispanic Kidney Transplant Program’s (HKTP) key culturally targeted components (outreach, communication, education) on Hispanic LDKT rates over five years. The main hypothesis is that exposure to the HKTP will reduce disparities by increasing the ratio of Hispanic to non-Hispanic white LDKTs and the number of Hispanic LDKTs. We will also examine other process and outcome measures including: dialysis patient outreach, education session attendance, marketing efforts, Hispanic patients added to the waitlist, Hispanic potential donors per potential recipient, and satisfaction with culturally competent care. We will use mixed methods based on the Promoting Action on Research Implementation in Health Services (revised PARIHS) and the Consolidated Framework for Implementation Research (CFIR) frameworks to formatively evaluate the fidelity and innovative adaptations to HKTP’s components at both study sites, to identify moderating factors that most affect implementation fidelity, and to identify adaptations that positively and negatively affect outcomes for patients.

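### H1 requires a rise in both the Hispanic:white LDKT ratio and the number of Hispanic LDKTs, but the stated test of H1 covers only the ratio

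*Protocol article*

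**What the plan says.** Under Study design overview, H1 has two parts joined by a conjunction: "Increase in the ratio of Hispanic to non-Hispanic white LDKTs and in the number of Hispanic" LDKTs. The abstract (Methods/Design) gives the same pair as the main hypothesis: "increasing the ratio of Hispanic to non-Hispanic white LDKTs and the number of Hispanic LDKTs".

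The Statistical analysis plan section then addresses H1 by name. It starts "To test hypothesis 1, we will use OPTN/UNOS data, to construct the ratio of the number of Hispanics receiving LDKTs" and sets that against the number of white recipients. It continues "An interrupted time series (ITS) design with segmented regression analysis will be used to assess the HKTP", and the input is described as follows: "Ratio data will be collected across 24 quarterly time points pre-intervention (reference point), and 14 time periods post-intervention".

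The number of Hispanic LDKTs appears in three other places.
- Table 2 lists it as a final outcome. Its change is to be compared with the change in white LDKTs, to show that any gain did not come at white patients' expense.
- The Discussion concedes that spill-over to white patients would favor the null hypothesis and names the Hispanic number as the safeguard.
- A general sentence covering H1 and H2 says that quarterly registry data "will be used to model ethnic and racial differences in transplants".

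**The concern.** A ratio of two counts can rise because the numerator rises or because the denominator falls. The second part of H1 separates these cases: it requires that more Hispanic patients actually receive a living donor kidney. If only the ratio is tested, a center whose white LDKTs decline after the program starts can be reported as meeting H1 although Hispanic LDKTs have not changed. For a study meant to increase Hispanic LDKTs, that would be a claim about the main hypothesis that half of its own wording does not support. The document gives no rule for what to conclude when only one part moves.

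**Working it through.** **1. The plan's own figure.** The plan uses "quarterly UNOS outcome data (6 years pre- and 3.5 years post-HKTP". Pre-period: 6 × 4 = 24 quarters. Post-period: 3.5 × 4 = 14 quarters. Total: 24 + 14 = 38, as stated. All 38 points are described as ratio data.

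**2. Hypothesis against test.**

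| Part of H1 | In the hypothesis | In the stated H1 test | Elsewhere |
|---|---|---|---|
| Ratio | yes | yes, segmented regression, 38 points | Table 2, final outcome |
| Number of Hispanic LDKTs | yes | no | Table 2, comparison of changes; Discussion, safeguard against spill-over |

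The general sentence on ethnic and racial differences describes a contrast between groups, not a test of the Hispanic number. The probabilistic sensitivity analysis concerns attribution of changes in LDKT volume and is not a test of H1 either.

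**3. How far the two parts can separate.** Let Hispanic LDKTs stay the same and white LDKTs fall by 30%. The ratio is multiplied by 1 / 0.70 = 1.43. For example, with 3 Hispanic and 9 white LDKTs per quarter, it goes from 3/9 = 0.333 to 3/6.3 = 0.476, a rise of 43% with no extra Hispanic LDKT.

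**4. How often the ratio test would then be positive.** The document gives no center volumes and no significance level for H1, so these inputs are assumptions:
- independent Poisson counts of 3/9, 5/15 or 10/30 Hispanic/white LDKTs per quarter;
- 24 + 14 quarters at one site, with no control site;
- least-squares segmented regression with a time trend and a level change;
- two-sided 5% test, counting significant increases in level.

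| Hispanic/white per quarter | Ratio test positive | Number test positive |
|---|---|---|
| 3/9 | about 10% | about 2% |
| 5/15 | about 18% | about 2% |
| 10/30 | about 34% | about 2% |

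Requiring both to rise also gives about 2%.

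**5. Other assumptions.** With 3/8, 5/12 and 8/20 per quarter, a 40% white decline and a Poisson model for the number, the trend-adjusted ratio test is positive in 17%, 27% and 44% of runs, against about 2% to 3% for the number. The size depends on the assumed volumes and decline; the direction does not.

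**The case against.** The strongest reply is that the number is not forgotten. It is a final outcome, Table 2 describes how its change will be set against the white change, and the Discussion assigns it to spill-over. The sentence introducing the interrupted time series is not expressly limited to the ratio, H2 is itself a count that receives no paragraph of its own, and an article may leave model forms to a full analysis plan. This stands to the extent that nobody should read the point as saying the number goes unmeasured or will not be analyzed. It does not remove the mismatch, because the article goes beyond omitting detail: it names the variable, the method and the number of points for H1, and these cover one of two parts. The Discussion's safeguard works only if the number counts when H1 is judged.

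A second reply is that matched controls are there to catch a secular or regional fall in white LDKTs, and the simulation has none. That is fair, and the percentages should be read as single-site figures. A decline confined to the intervention center would not be removed by the comparison.

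A third reply is that in the simulated case the ratio truly rises, so a positive ratio test is correct for the ratio. Also true: it misleads only when reported as H1.

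A reader might also infer the reverse error, that the ratio test would miss H1 when Hispanic and white LDKTs grow together. The documents do not support that. With both parts required, an unchanged ratio means H1 is false, and a silent ratio test is right. In a scenario with both groups up 50%, the both-must-rise rule declares H1 in about 2% of runs, the same as the ratio test alone.

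**Conclusion.** The point holds as a mismatch between the hypothesis as worded and the test stated for it. H1 could be declared from a fall in white LDKTs without any rise in Hispanic LDKTs. Under the assumed volumes and a 30% decline, this happens in about 10% to 34% of single-site series for the trend-adjusted ratio test, against about 2% when the number is tested. These figures rest on assumed volumes, independent Poisson counts and no control site, and the matched-control comparison may lower them. The point does not extend to saying that the number is absent from the study, or that H1 would be missed when both groups increase. It is worth correcting because it concerns the main hypothesis, but it is a modest change since the data are already planned.

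**What to change.** State that H1 is tested by two segmented analyses over the same 38 quarters at each center: one of the ratio, and one of the quarterly number of Hispanic LDKTs using a Poisson or negative binomial model. Declare H1, as worded, only if both rise. Because both tests must succeed, no adjustment of the significance level is needed.

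If only one part rises, report that part alone. A higher ratio without more Hispanic LDKTs is a change in relative share. More Hispanic LDKTs without a ratio gain, which is the spill-over case in the Discussion, is a gain in number. Neither is reported as H1 met.

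The cost is a few sentences and one extra model on counts already needed for the ratio's numerator. The drawback is that H1 becomes somewhat harder to declare than with the ratio test alone.
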